**Figure 3 F3:**
[figure not shown]
Study area (Source: Google Earth).

### Participant eligibility, recruitment, and retention

At the outset of the study, we will identify comparable communities associated with BMUs on the coast of Kilifi County using potential confounding variables: proximity to shoreline or ability to participate in the fishery; presence of no-take fisheries closures; composition of fishing gears used; background nutritional status; usual diets; income and assets; and access to market information. We will draw on existing relationships and data from communities where formative research was previously conducted by the project team. BMU leaders and other stakeholders will be convened to first inform them of the potential project and solicit permission to act in partnership with BMUs to conduct the research.

To be eligible to participate in the study, an individual must meet all of the following criteria:
A household member works in small-scale fisheries (self-employed fishers).At least one child in the household aged 6–60 months.Provision of signed and dated informed consent form.For children, informed assent and parental informed consent to participate in the study.Stated willingness to comply with all study procedures and availability for the duration of the study.

An individual who meets any of the following criteria will be excluded from participation in the study:
No household member works in small-scale fisheries (self-employed fishers).No child in the household aged 6–60 months.Declines to sign the informed consent.Index child is severely malnourished.Lives outside the study area.Participation in another nutrition or fisheries intervention study within April 2021 - June 2022.

We anticipate a total sample size of 400 small-scale fisher household units (mother, father, and child 6–60 months). There will be 100 in each intervention group (social marketing and social marketing plus modified traps) and 200 in the control group. Table 2 provides a summary of the total number of individuals and anticipated demographics.

**Table 2 T2:** Sample size and demographics.

**Group 1: Control (n = 200)**			**Group 2: Social marketing (n = 100)**			**Group 3: Social marketing + modified traps (n = 100)**		
**Group**	**# of individuals**	**Anticipated sex**	**Group**	**# of individuals**	**Anticipated sex**	**Group**	**# of individuals**	**Anticipated sex**
**Total sample size: 400 total households**								
Mother/caregiver	200	Female	Mother/caregiver	100	Female	Mother/caregiver	100	Female
Fisher	200	male	Fisher	100	Male	Fisher	100	Male
Children 6–60 months	Minimum of 200	Mixed	Children 6–60 months	Minimum of 100	Mixed	Children 6–60 months	Minimum of 100	Mixed

Participant recruitment and enrollment will be conducted by the two Kenyan partner universities (Egerton University and Pwani University). Pwani University, located in Kilifi County and on the coast, is well-positioned to be in continuous interaction with community stakeholders. The Kenya P.I. from Pwani has established relationships in Kilifi over many years of working there and teaches many university students from the neighboring fishing villages. Additionally, the US Co-P.I. from the University of Rhode Island (URI) has worked in this area for over 10 years conducting research on coral reef fisheries management and has long-term working relationships with fishers and BMU leaders. The Kenya Co-P.I. from Egerton University was involved in formative research along the coast and has made contacts with local health care workers and clinics for collecting data and measuring nutrition outcomes.

Recruitment efforts will begin with consultations with key community stakeholders including BMU leaders and board representatives; health care workers in local clinics; community health workers (CHVs); religious leaders; municipal administrators. With their agreement, communities will be matched based on the closest set of characteristics and assigned to control and intervention groups.

Retention efforts will be primarily carried out in tandem with the social marketing campaign. Activities to increase participant engagement – both in control and intervention groups – will include meetings, social gatherings, and project materials (e.g. T-shirts, flyers, lifejackets). These efforts are modeled from the Lulun Project in Ecuador (25) and adapted to the Kenyan context should help retain participants.

### Interventions

The 12-month *Samaki Salama* intervention introduces practices and technologies that build on existing community assets and expressed needs and preferences of small-scale fishers and their households. The first component of the intervention package, nutrition social marketing, is a novel approach to increase nutrition awareness across multiple stakeholders that draws on psychology, marketing, and communications disciplines (25). Distinct from conventional nutrition education interventions that tend to use more didactic approaches and standardized materials, this strategy draws heavily on contextual factors to identify key messages and delivery platforms. Nutrition-focused social marketing campaigns have been shown to promote active engagement of participants throughout the trial, high compliance to the intervention, sustained behavior change, and low losses to follow-up (26). The effectiveness of social marketing increases if targeted messages are repeated and delivered across different platforms (27) and previous studies indicate that 6 months of animal source food nutrition messaging may not be enough to sustain impact (28). Therefore, we propose a 12-month intervention period.

The nutrition social marketing approach will be developed in close collaboration with the social and behavioral change group at USAID Advancing Nutrition. The focus is on promoting four priority behaviors among infants, young children and women of reproductive age in SSF households: (1) caregivers feed fish to young children 6 months to 5 years daily; (2) caregivers feed an age-appropriate diverse diet, including fish, to children 6 months – 5 years daily; (3) caregivers wash hands and the child's hands with soap or ash before feeding; (4) fathers reserve and take home a small portion of fish for child each day. The social marketing plan and audience analysis, including all materials, messaging, and delivery platform relies on formative research conducted in the study area and piloting of materials prior to implementation. As shown in Table 3, messaging centered on the four priority behaviors will be delivered through diverse channels to mothers/caregivers, fathers, and leaders/members of local institutions. The plans to engage these participants groups reflects a multi-level approach to support improved feeding and care behaviors through individual, family, and community level change.

**Table 3 T3:** Social marketing campaign activities and materials.

**Activity**	**Delivered by**	**Branded products**
**Mothers/caregivers**		
Personalized home visits	Staff (Home visitors); CHV	Reminder poster on home actions Letter to fathers about home action Calendar with child growth visual T-shirts Khanga cloth Story book
Cooking demonstrations	Staff; CHVs	Menu game about nutrition foods for children
**Fathers/fishers**		
Workshop series at fish landing sites	Staff	Commitment letter for fishing and home actions T-shirts Stickers Life jackets
**Institutions**		
BMUs orientations	Staff	Banners Posters Stickers
Health worker orientations	Staff, CHVs	Posters Stickers Bags

*Home visits* are a key component of the social marketing campaign and will occur at a three time points (3, 6, and 9 mo.) in both intervention groups. All homes in the intervention groups (*n* = 200) will be visited at each time point. Visits every 3 months will allow the field team enough time to complete one round of visits before starting the next round. Three visits per household is the maximum the field team anticipates being able to complete within the 12-month intervention. During visits, the team's nutrition education specialists will actively engage with the caregiver and child/children to build a positive relationship, understand their individual needs, and foster change. The suite of social marketing materials available to the field team will be the same for all intervention households but we anticipate that the exact information and materials provided will be tailored to meet the needs of the individual household and child/caregiver dyad. The nutrition team will discuss and identify illnesses before introducing age and stage-specific child feeding and hygiene habits (or recommendations) and help caregivers identify next steps and agree on actions geared toward improving feeding and hygiene practices and better health care. The overarching message caregivers will receive is that fish can be a critical source of nutrients for their child and paying special attention to their child's growth and development now has life-long benefits. Discussions, agreements, and actions taken will be documented and tracked by the nutrition team. Local CHVs in both intervention and control communities will be trained to conduct the home visits so caregivers will have a reliable source of information and support even after the project is completed.

Fifteen *cooking demonstrations* will be conducted in intervention communities with an anticipated 10–15 caregiver participants and their children per demonstration. The demonstrations will provide an overview of key nutrition concepts, important nutrients found in fish, and different approaches for fish preparation. Participants will be asked to plan a meal and snacks for their children using a “star foods” menu game and work together to prepare a fish centered meal. Questions will be asked at the beginning and end of the demonstration to better understand participants' nutrition knowledge, what they gained from the demonstration, and feedback for improving future demonstrations. Demonstrations will be conducted in local community spaces identified by the field team.

The project nutrition team will work together with the fisheries team to conduct a series of 10 *fisher workshops* at local BMU offices with fishers in both intervention groups. Table 4 provides a summary of the themes and topics that will be covered at each workshop.

**Table 4 T4:** Themes and topics of fisher workshops.

**Workshop theme**	**Intervention group**	**Discussion topics**
“We provide for our families”	Social marketing + modified traps	What it means to fishers to provide for their families Challenges they face providing for their families Benefits of using modified traps for income, their families nutrition, and fishery sustainability Commitment to using modified traps
	Social marketing	What it means to provide for their families Challenges they face providing for their families Stages of fish growth Activity to estimate mature size of common fish Reasons to focus on catching more mature fish Commitment to catch more mature fish
“We protect our families and communities”	Social marketing + modified traps	Check in on use of modified traps Hopes they have for their children Actions they can take to protect their children's health Encouraging each other to protect their children's nutrition Commitment to bring home some of their catch for their children
“We bring our BMU community”	Social marketing + modified traps	Check in on use of modified traps Refresh knowledge of child nutrition Discuss changes they have noticed in the areas where they fish (environment, fish quantity, fish types etc.) Importance of sharing the information they have received with other fishers Activity to develop a persuasive argument to protect the places where they fish and their children's nutrition Commitment to share what they have learned with new fishers and friends

Fisher training, gear modification, and fishing trap distribution constitute the second piece of the intervention. The use of fishing gears modified to decrease juvenile catch has been shown to lead to greater catch diversity and improve the economic value of fishes (16). Second, fishers can gain a competitive advantage when using new gears by fishing new habitats to catch previously targeted species in novel ways (15). This can reduce the impact of fishing on the environment, and in the case of coastal Kenya, coral reefs. Last, gear modifications have been shown to improve harvest efficiency and promote sustainable fish populations by selecting for mature individuals while at the same time improving fisher revenue (29). Using these rationales, our intervention targets fishers using basket traps and provides them with traps modified with escape gaps so immature fish can escape. Trap distribution will occur at landing sites utilized by participating fishers and at local BMU offices. The fishers will also receive training on how to properly maintain the traps they receive. We hypothesize this type of intervention will reduce fishers' dependence on immature fishes, as well as buffer them from potential market variability (30) and enable them to be more resilient to environmental change (31).

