The intervention will target communities matched based on location (rural), livelihoods, and child nutritional status. The matched sample will be divided into three groups: (1) control (*n* = 200); (2) multi-component nutrition social marketing intervention to fishers, mothers, and health workers (*n* = 100); (3) multi-component nutrition social marketing intervention plus modified fishing traps with escape gaps and training (*n* = 100). Although our original design was to have two comparison groups with equal numbers, formative research showed insufficient numbers of fishers currently using traps that could be recruited to use modified traps. Further, budgetary constraints precluded distributing traps to all 200 in the intervention group. Thus, we split the intervention group enabling us to test the added effects of modified traps together with social marketing. Figure 2 provides an overview of the study design and implementation process.

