**Figure 2 F2:**
[figure not shown]
Study design.

Both process and impact evaluations will be carried out using mixed methods. Primary and secondary nutrition outcomes include longitudinal difference-in-difference analyses of parameters – height-for-age *Z* score, stunting prevalence, child fish food intake, child dietary diversity, and child diarrheal morbidity. Other outcomes include awareness of the social marketing campaign and knowledge transfer. Primary and secondary fisheries outcomes will be longitudinal difference-in-difference analyses in fisheries yield of mature fish and fisher income and earnings.

The *Samaki Salama* intervention precludes randomization due to the high risk of spill-over effects and the limited number of trap fishers with children under the age of 5. Thus, for the impact assessment, we will conduct a matched intervention/control design to minimize selection bias and test effectiveness on nutrition and fisheries production. Steps have been taken to reduce the risk of selection bias that might arise from the matched design. A pilot study and additional formative research will be used to identify and match communities on important characteristics [socioeconomic status (SES), child nutrition, livelihoods, etc.]. This preliminary data provides additional information needed for external validity and extrapolation of findings to other small fisher households in Kenya and internationally. The longitudinal difference-in-difference design further contributes to the internal validity, accounting for residual confounding, and increases the statistical power to detect intervention effects.

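### Health volunteers in control communities are to be trained for the campaign's home visits with no deferral past endline, so control households could receive part of the messaging

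*Protocol article*

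**What the plan says.** All references are to the protocol article.

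- **Interventions, home visits.** The visits "are a key component of the social marketing campaign and will occur at a three time points". The schedule covers intervention households only: visits "will occur at a three time points (3, 6, and 9 mo.) in both intervention groups". The same paragraph then says "Local CHVs in both intervention and control communities will be trained to conduct the home visits", and gives the purpose: "so caregivers will have a reliable source of information and support even after the project is completed".
- **Table 3.** Community health volunteers (CHVs) are listed among those who deliver the home visits and cooking demonstrations. Orientation of health workers is itself a campaign activity.
- **Design.** The intervention is defined as a "multi-component nutrition social marketing intervention to fishers, mothers, and health workers". A later paragraph of the same section says the intervention "precludes randomization due to the high risk of spill-over effects", with the small number of eligible trap fishers as a second reason.
- **Participant eligibility, recruitment, and retention.** "Retention efforts will be primarily carried out in tandem with the social marketing campaign". The activities, "both in control and intervention groups – will include meetings, social gatherings, and project materials (e.g. T-shirts, flyers, lifejackets", apply to controls too. T-shirts and life jackets also appear in Table 3 as branded campaign products. Flyers do not.

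**The concern.** The active ingredient of the social marketing arm is information on feeding fish, diverse diets and handwashing. A CHV trained to run the home visits can pass that information on. Training such people in control communities during the 12 months would open a route by which controls receive some of what the trial tests. Because health workers are a named target of the intervention, the training also overlaps with one of its channels before any household is visited.

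This sits badly with the Design section, which accepts a non-randomized comparison partly because of spill-over.

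Hypotheses 1 to 5 (HAZ, WAZ, fish intake, dietary diversity, diarrhea) all compare the combined intervention groups with control. Exposure of controls before endline would be expected to pull these contrasts toward zero and to make a null result harder to read.

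**Working it through.** **1. Is control exposure planned, excluded or left open?**

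| Element | Intervention communities | Control communities |
|---|---|---|
| Scheduled home visits (months 3, 6, 9) | Yes, 200 households | Not scheduled |
| Cooking demonstrations | Yes | Not scheduled |
| Fisher workshops | Yes | Not scheduled |
| CHVs trained for home visits | Yes | Yes, undated |
| Retention meetings, gatherings, T-shirts, flyers, lifejackets | Yes | Yes, content not described |

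The stated purpose, support that continues even after the project, reads most naturally as during and after. The article neither defers the control training nor bars trained control CHVs from visiting before endline. Exposure is therefore possible under the plan as written, but it is not scheduled.

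**2. Does difference-in-difference remove it?** No. Let f be the share of the intervention effect that also reaches controls after baseline. The expected estimate is

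(change in intervention) − (change in control) = 0.20 − f × 0.20 = 0.20 × (1 − f).

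The exposure arises between the two surveys, so it enters the control group's change and is not differenced out.

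**3. The plan's own figure.** The Sample size section gives 400 households for a 0.20 HAZ effect, α = 0.05, power 0.80 and 20% loss. It states neither the SD nor the intracluster correlation, so 400 cannot be reproduced from the stated inputs. With 200 against 200 enrolled, 160 against 160 remain after 20% loss. With no clustering, 80% power then implies an SD of about 0.64 (two-sided) or 0.72 (one-sided). The next step does not need these values: it takes the 80% target as given.

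**4. Illustration of dilution (f is assumed; the document gives no basis for any value).** By normal approximation, with the undiluted test set to 80% power:

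- One-sided 0.05, the test named in the Analysis section: power = Φ[(1.645 + 0.842)(1 − f) − 1.645]
- Two-sided 0.05: power = Φ[(1.960 + 0.842)(1 − f) − 1.960]
- Sample size multiplier to restore 80%: 1/(1 − f)²

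For f = 0.25, one-sided: 2.487 × 0.75 − 1.645 = 0.220, and Φ = 0.587. Two-sided: 2.802 × 0.75 − 1.960 = 0.141, and Φ = 0.556.

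| f (assumed) | HAZ difference | Power, one-sided | Power, two-sided | Multiplier |
|---|---|---|---|---|
| 0 | 0.20 | 80% | 80% | 1.00 |
| 0.10 | 0.18 | 72% | 71% | 1.23 |
| 0.25 | 0.15 | 59% | 56% | 1.78 |
| 0.50 | 0.10 | 34% | 29% | 4.00 |

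**The case against.** The strongest reply is that training is not delivery. Visits, demonstrations and workshops are all assigned to the intervention side, and nothing in the article sends a trained CHV to a control household. The stated purpose of the training looks toward continuity beyond the project. A journal article may also leave the training calendar to the full protocol. This stands as far as it goes. A reader might infer that the control arm does receive part of the intervention and that the estimate is biased, but the text supports only a possible exposure whose timing is not fixed. It is still more than an omitted detail, because the article affirmatively includes control communities in the training for a key campaign component.

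The materials are the weaker part. Only T-shirts and life jackets overlap with Table 3. The plainly message-bearing items there (reminder poster, letter to fathers, story book, menu game) are not named for controls. Retention incentives in both arms are a legitimate guard against differential attrition, and T-shirts or life jackets alone may do little for growth.

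Two further inferences fail. Not every Aim 1 contrast is affected, because Hypothesis 6 compares the two intervention groups with each other. Nor would a null result be uninterpretable: Table 6 has awareness and knowledge measured at baseline and 12 months, so control exposure could be examined. Dilution would also be conservative and would not create false positives. It would still cost power.

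**Conclusion.** The point holds in conditional form. The plan trains control-community CHVs for the campaign's home visits without deferring this past endline, and gives controls retention meetings and materials whose content is not described. If the training precedes the 12-month survey and those CHVs pass on the messages, the contrasts in Hypotheses 1 to 5 are expected to shrink toward zero. If the training follows endline, this route causes no bias.

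The size is unknown. The illustration (25% dilution: 0.20 becomes 0.15, and power falls from 80% to about 59% one-sided or 56% two-sided) rests on an assumed share and on the protocol's nominal 80% power, which cannot be verified without an SD and an intracluster correlation. It shows sensitivity and is not an estimate. Contamination cannot be undone once the training has taken place, so the timing needs to be fixed beforehand.

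**What to change.** 1. State under Interventions that CHVs in control communities are trained, and make any campaign visits, only after the 12-month endline survey.
2. State under retention that meetings and materials for controls carry no campaign brand and no nutrition or fishing message.
3. Report control-arm exposure from the awareness and knowledge items already in the baseline and 12-month household/fisher survey, alongside the results for Hypotheses 1 to 5.

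The cost is small: one training is rescheduled and some control retention items may need replacing. No new data collection is needed. The downside is that control communities receive the training later.

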## Methods and analysis

### Design

We aim to test the effectiveness of the multi-component *Samaki Salama* intervention as it intersects with nutrition security and fisheries sustainability in Kilifi County, Kenya. Table 1 details the specific aims and hypotheses.

**Table 1 T1:** Study aims and hypotheses.

**Study aims**	**Hypotheses**
1. Determine the effects of a multi-component social marketing campaign to promote fish nutrition, dietary diversity, and food safety on child growth	**Primary** Hypothesis 1: Children in combined intervention groups have increased height-for-age *Z* by 0.2 compared to children in the control Hypothesis 2: Children in combined intervention groups have increased weight-for-age *Z* by 0.10 compared to children in the control Hypothesis 3: Children in combined intervention groups have increased fish food intakes by 100 g compared to children in the control
	**Secondary** Hypothesis 4: Children in combined intervention groups have increased dietary diversity by 1.2 compared to children in the control Hypothesis 5: Children in combined intervention groups have reduced diarrheal morbidity by 5 percentage points compared to children in the control
	**Exploratory** Hypothesis 6: Children in the social marketing + traps intervention group have increased dietary diversity and fish intake compared to children in the social marketing only group
2. Measure the impact of modified fishing traps with escape gaps on catch dynamics and earnings	**Primary** Hypothesis 7: Fishers in the social marketing + traps intervention group have significantly increased fisheries yields of mature fish compared to fishers in the control
	**Secondary** Hypothesis 8: Fishers in the social marketing + traps intervention group will have significantly increased earnings compared to fishers in the control

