### Analysis

#### Primary and secondary outcomes

Generalized linear regression modeling (GLM), allowing for non-normal distributions, will test the continuous outcomes of HAZ, WAZ, child dietary fish intake, child dietary diversity score, fisheries yield, and fish earnings. As a difference-in-difference analyses, change variables for each outcome will be examined (difference between baseline and endline). For the binomial outcomes of diarrhea morbidity (and other outcomes of stunting and underweight), we will estimate prevalence ratios by the GLM modeling with robust Poisson. If stunting prevalence in this population exceeds the acceptable threshold for use of odds ratios (0.2105), prevalence ratios (PRs) will be used to examine the intervention effect and were considered analogous to relative risk in this longitudinal study. The robust Poisson, with a classic sandwich estimator to correct the inflated variance of standard Poisson, is less affected by outliers.

To test for intervention effectiveness, the two intervention groups will be combined for all hypotheses except the secondary outcome of increased fisher earnings and exploratory hypothesis for differences between social marketing and social marketing + traps intervention groups. Regression models will be adjusted for potential confounding factors including age, sex of the child, corresponding baseline measures, and others found to differ significantly between the trial groups (e.g., maternal education). For fisheries yield, confounding factors will be used to adjust regression models, such as: water temperature, fishing ground area, coral cover, and seasonality. The *P* significance value for Type I error (and one-tailed test) will be *P* < 0.05 and corresponding 95% confidence interval. Diagnostics for regression model assumptions, structure and observations will be applied, and corrective procedures applied as necessary. If selection bias is widely detected with important differences across intervention and control communities, we will apply propensity score analyses (36). Data analyses will be performed with Stata software (version 16.0; StataCorp, College Station, TX) and R (4.1.2).

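### H7 and H8 set basket-trap fishers in group 3 against control fishers of any gear, and baseline gear is not a named adjuster, so gear is confounded with group at fisher level

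*Protocol article*

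**What the plan says.** Aim 2 in Table 1 is to measure what modified traps do to catch and earnings. H7 reads: "Fishers in the social marketing + traps intervention group have significantly increased fisheries yields of mature fish compared to fishers in the control". H8 reads: "Fishers in the social marketing + traps intervention group will have significantly increased earnings compared to fishers in the control".

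For the trap component, Interventions states that "our intervention targets fishers using basket traps and provides them with traps modified with escape gaps so immature fish can escape". The Design section explains the three-arm split by noting that "formative research showed insufficient numbers of fishers currently using traps that could be recruited to use modified traps".

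Under Participant eligibility, the only fishing criterion is: "A household member works in small-scale fisheries (self-employed fishers". It applies to all groups and says nothing about gear. The same section lists the gear mix of a community among the characteristics used to find comparable communities.

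The Analysis section gives as examples of adjusters for yield: "water temperature, fishing ground area, coral cover, and seasonality". It gives no list specific to earnings. It also allows adjustment for variables that differ significantly between groups, and propensity score analysis if important differences appear. On pooling, it says that "the two intervention groups will be combined for all hypotheses except the secondary outcome of increased fisher earnings" (the exploratory comparison of the two intervention groups is the other exception).

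**The concern.** Gear helps to decide which species and sizes are caught. The protocol treats it as important: it is used in choosing communities, it is considered in planning catch sampling, and the case for the intervention rests on a gear modification changing maturity of catch and revenue. Yet where fishers are compared, one side is aimed at basket-trap users and the other is open to any gear, with no stated provision for the difference.

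H7 is a primary hypothesis. If trap catches and other catches move differently over the study year, for instance because a season or a shift in stocks affects them unequally, that divergence would enter the group 3 versus control contrast and could be read as an effect of the intervention. It could equally hide a real effect. Adjusting for seasonality as a main effect removes a seasonal shift common to all gears, but not one that differs by gear.

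**Working it through.** The documents give no effect size, SD or power for H7 or H8, so there is no stated figure to reproduce. The check has three parts.

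**1. Does community matching remove the imbalance?** Take two communities with the same share p of trap fishers. If group 3 fishers are drawn from the trap users and control fishers from everyone, the trap share is about 1 in group 3 and p in control. Equal gear mix at community level leaves an imbalance of 1 − p between the fishers compared. Taking group 3 as entirely trap users is an assumption at the upper end: the text says that they are targeted, not that each one used traps at baseline.

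**2. What does differencing leave?** Let traps change by c_T and other gears by c_O from before to after, with no intervention effect.

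- Expected change in group 3: c_T
- Expected change in control: p·c_T + (1 − p)·c_O
- Difference: (1 − p)(c_T − c_O)

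A constant gap between gears cancels; a gap that changes does not. This holds only with a true pre-intervention period. Study measures places the fisheries measurements within the 12 intervention months, and Table 5 lists sampling over those months with no baseline for yield or earnings, although it lists a baseline for the nutrition outcomes. Fisher revenue speaks of change from before to after the intervention without saying when the earlier data are collected. Without a pre-period, the level gap between gears would not be differenced out.

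**3. How sensitive is the test?** This is an illustration, not an estimate. Write D for the gear difference left in the contrast, in SD units, taken to favour traps. Assume no true effect, independent fishers, and 20% loss (borrowed from the height-for-age sample size), leaving 80 versus 160. The one-tailed 0.05 level is the protocol's.

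SE = √(1/80 + 1/160) = 0.137. False-positive probability = Φ[(1 − p)D/SE − 1.645].

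| Trap share in control, p | D = 0.25 | D = 0.5 |
|---|---|---|
| 0.10 | 0.50 | 0.95 |
| 0.25 | 0.39 | 0.86 |
| 0.50 | 0.23 | 0.57 |
| 1.00 | 0.05 | 0.05 |

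Example: p = 0.25 and D = 0.25 give 0.75 × 0.25 = 0.1875; 0.1875/0.137 = 1.37; Φ(1.37 − 1.645) = 0.39. With D = 0 every cell is 0.05. If D runs the other way, the test becomes conservative and a real effect may be missed. Both p and D are assumed.

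**Effect of pooling.** If H7 were tested on groups 2 and 3 together, as the Analysis section says, and group 2 had the same trap share as control, the pooled share would be (1 + p)/2 and the imbalance (1 − p)/2, half as large. The trap effect would be diluted too, since 100 of the 200 pooled fishers receive no traps. H8 is exempt from pooling and keeps the full imbalance.

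**The case against.** The strongest case against has four parts.

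- **The analysis is difference-in-difference.** This is right, and it removes stable gear differences. It does not remove gear-specific change, and the catch data that it needs from before the intervention are not shown.
- **Some comparisons are at site level.** Fisher revenue describes comparing earnings by landing site or beach management unit, close to the level at which gear mix is matched. This has weight: averages over all landings at well-matched sites would be less exposed. But H8 is worded for the fishers in each group, and an average over all landings is a different quantity from the one in Table 1.
- **The adjuster list is open, and an article may leave the full list elsewhere.** The list is indeed given as examples, and gear could enter through the rule on significant differences or through propensity scores. Gear is not an incidental covariate, however; the way group 3 is recruited builds the imbalance in. Its inclusion should not hang on a significance test.
- **Restricting to trap trips has its own flaw.** This stands. Gear on a sampled trip is chosen after traps are distributed and commitment to use them is sought, so conditioning on it conditions on something that the intervention can change. Gear should be classified at baseline.

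A reader might also infer that most control trips use other gears. The documents say only that trap users available for recruitment were too few; they give no trap share for control communities.

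**Conclusion.** The point holds as a fisher-level confounding by gear in the Table 1 contrasts, unaddressed by any named adjuster and only partly protected by matching and differencing. It applies in full to H8, and to H7 if Table 1 governs. If the Analysis section governs H7, the imbalance is diluted, and the two statements conflict in any case.

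The documents do not allow the size to be derived. A reader might multiply an assumed share of non-trap trips by an assumed gap in yield, such as 0.8 × 50% = 40%, and call that the bias. Both inputs are assumed, and the product is a bias in levels, whereas the stated analysis is of change. The false-positive rates above show only that a residual gear difference of 0.25 to 0.5 SD would matter; nothing in the documents says that one of that size exists.

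Nor would settling the gear question isolate escape gaps. Group 3 also receives social marketing, so even a contrast between trap fishers estimates the package.

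**What to change.** 1. Name each fisher's main gear before the intervention as a required adjuster or stratum in the H7 and H8 models, whether or not it differs significantly between groups.
2. Add, as a supporting analysis, group 3 against control fishers who used basket traps at baseline. Classify by baseline gear, not by gear on the sampled trip.
3. State the pre-intervention period from which baseline catch and earnings come.
4. Reconcile Table 1 with the Analysis section on whether H7 uses group 3 alone or groups 2 and 3 combined.
5. State that the group 3 contrast estimates social marketing plus traps together.

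The cost is mainly wording. The baseline household and fisher survey already covers fishing characteristics; if main gear is not among them, one item is needed. The statistical cost is precision if few control fishers use traps. For the supporting comparison, under the same assumptions as above, 160 control fishers with trap shares of 0.50, 0.25 and 0.10 leave 80, 40 and 16. The SE becomes √(1/80 + 1/80) = 0.158, √(1/80 + 1/40) = 0.194 and √(1/80 + 1/16) = 0.274, against 0.137 with all controls. That loss is why this comparison is proposed as support and not as the main test.
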